#### Socio-demographic variables

Socio-demographic variables that were measured included highest completed level of education, marital status, work situation, native country, presence of diabetes, smoking behavior [73,110], alcohol consumption [111], family history of cardiovascular disease, and stress [112]. In addition, the Physical Activity Readiness Questionnaire (PAR-Q [113]) was used to assess barriers to participation in physical activity, for example, chest pain during physical activity or bone or joint problems.

Gender, hypertension status and age were used as variables for selecting participants from the GP database and these data were provided by the GP only when participants agreed to participate. The other socio-demographic variables were measured at baseline; smoking behavior and alcohol consumption were also measured at both follow-ups (47 and 73 weeks after baseline).

### Statistical analyses

#### Sample size and power

The required sample size was determined using the formula for unpaired *t*-tests [114], as each effect test in a balanced 2 × 2 between-subject design (i.e., the TMI and the TPC main effects and their interaction) comes down to such *t*-tests (apart from having less residual variance). The sample size calculation was based on the following assumptions: (a) since results of similar studies were not available at the start of Vitalum, the sample size calculation was based on a small expected effect size (Cohen's d) of .3 [115]; (b) a power of .9; (c) an alpha of .01 to correct for multiple testing; (d) an intra class correlation of .02, where the correlation is based on random treatment by GP interaction (a random GP main effect does not affect the sample size in the event of person randomizations within GPs) [116]; and (e) an expected average number of participants per general practice of 70. Loss of power due to random dropout or a gain in power from including the pretest as a covariate in the analyses [117] was not taken into account in the sample size calculation. However, the loss of power due to 20% random dropout can be compensated by including the pretest as a covariate if it correlates .5 with the posttest – the latter correlation being a realistic assumption. These assumptions resulted in a required sample size at baseline of 1,600. Thus, Vitalum aims to assess 400 participants per group at baseline. Assuming 50% of people refuse participation, and 40% of the remaining group meet the recommendations for PA and nutrition and are thus excluded, at least 5,400 people must be invited to secure 1,600 for the study.

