3. The combined group (TPC+TMI), in which participants received two tailored print letters and two telephone motivational interviews in turns. The first letter and call addressed PA; the second letter and call focused on fruit and vegetable consumption. Participants could also choose to discuss fat intake in the fourth call. The total number of intervention components (4) was kept to a similar total number as that of the first two groups. Also, we exposed participants to an equal amount of each intervention type (2*TPC, 2*TMI) to keep the influence of both methods as comparable as possible.

4. The control group, in which participants received one tailored letter based on the last follow-up questionnaire.

Participants from the three intervention groups received their four intervention components at 5, 13, 30 and 43 weeks after they had returned the baseline questionnaire. This timeframe was chosen to spread delivery of the components throughout the year [48]. Vitalum used a two-way design (TMI * TPC) except for the fact that the combined group received half of each treatment type (2*TPC and 2*TMI instead of 4*TMI and 4*TPC). The study design and timeline is depicted in Figure 2.

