#### Hypotheses

Effect size estimates for our intervention and control conditions were difficult to determine, because similar studies were not available at the start of Vitalum (2003). However, one study on MI [48] and others on computer tailoring [27,33,40] found increases of at least 10% in one or more of the target behaviors (i.e., PA, fruit or vegetable consumption, or saturated fat intake) in participants who received single or multiple MI or tailoring compared to control group participants. As PA and fruit and vegetable consumption will receive more attention than saturated fat intake, we also expect to find larger effects for these. Therefore, we formulated the following hypotheses:

1. Compared to those in the control group, participants receiving either TMI or TPC will (a) increase PA as well as fruit and vegetable intake by 10% at the first follow-up from the expected mean at baseline; and (b) decrease saturated fat intake by 5%.

2. Participants receiving TPC+TMI will have resulting behavioral changes which exceed the sum of the changes expected given each intervention.

3. Participants with a low education level benefit more from TMI than TPC.

4. Participants without hypertension benefit more from TMI than TPC.

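### The total of 1,600 gives 90% power for an 800 v 800 factorial margin; Hypothesis 1 compares single arms of 400 with control, where power for d = .3 is about 76%

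*Protocol article*

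**What the plan says.** Sample size and power (protocol article): "The required sample size was determined using the formula for unpaired" t-tests. The reason given is that such a test underlies "each effect test in a balanced 2 × 2 between-subject design (i.e., the TMI and the TPC main effects and their interaction". The inputs are "a small expected effect size (Cohen's d) of .3", power .9, "an alpha of .01 to correct for multiple testing", "an intra class correlation of .02" arising from treatment-by-practice variation, and 70 participants per practice. The result is 1,600 in total: "Thus, Vitalum aims to assess 400 participants per group at baseline". A dropout of 20% is left out of the total, on the ground that a pretest covariate correlating .5 with the posttest can make up for it.

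Study design (after Table 1) calls the design two-way "except for the fact that the combined group received half of each treatment type (2*TPC and 2*TMI instead of 4*TMI and 4*TPC".

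Hypothesis 1 begins "Compared to those in the control group, participants receiving either TMI or TPC will" and expects improvement in each behaviour. Hypothesis 2 deals with the combined arm separately. The outcome-analysis section enters intervention group as an independent variable. The article gives no sample size or power for a single arm against control.

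**The concern.** A factorial sample size is economical because every participant contributes to each main effect. That requires the combined cell to hold full TMI plus full TPC, and here it holds half of each. It also requires the hypotheses to concern the margins, whereas Hypothesis 1 concerns single arms against control, with half the participants.

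The 90% is the only power the article states, so readers will apply it to its first hypothesis. A null result for TMI or TPC against control would then be judged against a power which that comparison did not have. If margins were tested instead, the result would mix the combined arm with the single arms and could be mistaken for the effect of one treatment.

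**Working it through.** **Reproducing 1,600.** Per side, n = 2(z₀.₉₉₅ + z₀.₉₀)²/d² = 2(2.576 + 1.282)²/0.3² = 331. The design effect is 1 + (70 − 1) × .02 = 2.38. The total is 2 × 331 × 2.38 = 1,576 (1,574 without rounding), close to 1,600. A one-sided test gives 2 × 290 × 2.38 = 1,380, which does not fit. Sizing for arm v arm (two-sided) does not give 1,600 either: 4 × 331 × 1.33 = 1,761, × 1.68 = 2,224 and × 2.38 = 3,151. So 1,600 is the total for one comparison of 800 with 800.

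**Power formula.** z = d/√(2 × DE/n) and power = Φ(z − 2.576), with n per side and DE the design effect. For 800 v 800, d = .3 and DE 2.38, z = 3.89 and power is 90.5%, as planned.

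**What the margin estimates.** Let T, P and C be the effects of TMI, TPC and combined against control, in SD units. The TMI margin is (T + C)/2 − P/2 = (T + C − P)/2. It equals T only if C = T + P. With T = P = .3, at 800 v 800 and DE 2.38:

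| Combined effect C (assumed) | Margin | Power |
|---|---|---|
| .6 | .30 | 90.5% |
| .45 | .225 | 63% |
| .3 | .15 | 26% |

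The article does not give C, so this table is conditional on an assumption about the half-dose arm.

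**Hypothesis 1: 400 v 400, d = .3.** The 70 per practice counts all four arms (1,629/23 = 70.8). Two arms have about 35 per practice, so DE = 1 + 34 × .02 = 1.68. If the ICC is applied to a single arm within a practice (17.5), DE = 1 + 16.5 × .02 = 1.33. The effect detectable with 90% power is 3.857 × √(2 × DE/400).

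| Design effect | z | Power | Detectable d |
|---|---|---|---|
| 1.33 (17.5 per practice) | 3.68 | 86% | 0.31 |
| 1.68 (35 per practice) | 3.27 | 76% | 0.35 |
| 2.38 (carried over unchanged) | 2.75 | 57% | 0.42 |

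With no clustering at all, power would be 95%, so the shortfall comes from the plan's own ICC.

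**With the plan's dropout and covariate.** Take 320 per arm, residual variance × (1 − .5²) = 0.75, and practice size cut by 20%.
- 28 per practice in two arms: DE = 1 + 27 × .02 = 1.54, z = .3/√(2 × 1.54 × 0.75/320) = 3.53, power 83%, detectable d 0.33.
- 14 per arm per practice: DE = 1 + 13 × .02 = 1.26, z = 3.90, power 91%.
- With practice size not reduced (DE 1.68 or 1.33), power is 79% or 89%.

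**The case against.** Several points on the other side stand.

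- The article expects the combined arm to do best, and Hypothesis 2 expects it to exceed the sum of the separate effects. If that sum means the two single-arm effects, the margin keeps its 90% power. A reader might infer from the 26% row that the factorial tests are hopeless. The article does not support that, because the row assumes the combined arm is no better than one treatment alone.
- A reader might take 57% as the power for Hypothesis 1. It applies a four-arm practice size to a two-arm comparison, so it is an extreme and not a central value.
- With the plan's dropout and covariate, power is about 83%, and the most lenient reading of the ICC reaches 91%. As d = .3 is a conventional small effect chosen for want of comparable studies, a detectable effect of 0.33 to 0.35 is a modest loss.
- The analysis section enters intervention group and specifies no margin test, and the half-dose arm is openly disclosed. It cannot be said that the trial will report margins as treatment effects. Nor does lower power bias an arm v control estimate or raise its type I error.

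These points limit the size but leave the mismatch. Under Hypothesis 2 the margin's power would depend on the very synergy to be tested, and a significant margin could come from the combined arm alone, so it would not establish Hypothesis 1. The powered interaction is the term nearest to Hypothesis 2, but the half-dose cell keeps it from being a clean test. The article format is no excuse, since formula, inputs, contrasts and total are all stated.

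**Conclusion.** The point holds, with a moderate size. The figure of 1,600 is arithmetically right for a balanced factorial margin, but it is not matched to Hypothesis 1. For a single arm against control at d = .3, power is about 76%, on the assumptions of a two-sided alpha of .01, ICC .02 and 35 participants per practice across two arms. The range by design effect is 57% to 86%. With the plan's dropout and covariate and practice size reduced to match, it is about 83%, or about 91% on the most lenient ICC reading. This shortfall needs no assumption about dose-response. What a margin test would deliver does need one: 90.5%, 63% or 26% as the combined effect is .6, .45 or .3.

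**What to change.** In Sample size and power, keep the 90% for the factorial margin only, with the condition under which that margin equals a single-treatment effect. For Hypothesis 1, state the arm v control power: about 76% for d = .3, or 90% for d of about 0.35, with the design effect of 1.68 and its basis given. If the dropout and covariate argument is kept, show its result for this contrast.

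In the outcome analyses, say that intervention group is a four-level factor, as the text already implies, with TMI v control and TPC v control as the contrasts for Hypothesis 1. Do not report factorial main effects as the effect of TMI or TPC.

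The cost is a less favourable stated power. Recruitment, allocation and conduct do not change.

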	**%/Mean, SD (range)**
Gender	
% male	55
Age	57.1, 7.1 (44.9–70.9)
Native country	
% the Netherlands	95
Education level*	
% low	54
% intermediate	23
% high	23
Hypertension	
% Hypertensive	52
Body Mass Index	27.4, 4.6 (15.2–46.7)
% < 18.5	1
% 18.5–25	31
% 25–30	45
% >= 30	22
Smoking behavior	
% nonsmokers	78
Alcohol consumption**	
Glasses/day	1.1, 1.4 (0–9)
% meeting guideline	86
Saturated fat intake	
Fat score	17.8, 5.9 (2–37)
% meeting guideline	30
PA	
Hours/week moderately physically active	4.7, 3.8 (0–20.2)
% >= 2.5 hours/week moderately physically active	61
Days/week moderately physically active	2.2, 1.6 (0–7)
% >= 5 days/week moderately physically active	6
% meeting guideline combined	0
Fruit consumption	
Pieces of fruit/day	2.1, 1.6 (0–8.9)
% >= 2 pieces/day	41
Days/week at least 2 pieces/day	3, 2.5 (0–7)
% >= 7 days/week at least 2 pieces/day	13
% meeting guideline combined	11
Vegetable consumption	
Grams of vegetables/day	165.2, 82.4 (0–494.7)
% >= 200 grams/day	31
Days/week at least 200 grams/day	4.1, 2.0 (0–7)
% >= 7 days/week at least 200 grams/day	11
% meeting guideline combined	7

* Education level was classified as: low in participants with no education, primary, lower secondary vocational, preparatory vocational or junior general secondary education; intermediate in participants with senior secondary vocational, technical secondary, upper vocational secondary, senior general secondary or university preparatory education; and high in participants with higher professional or university education [125-127].

** Participants were classified as meeting the alcohol consumption guideline if they consumed fewer than 3 glasses a day (men) or fewer than 2 glasses a day (women) [10].

Participants were stratified and randomized into the following four groups by a computer program.

1. The tailored print communication (TPC) group, in which participants received four tailored letters. The first and third letter focused on PA, the second and fourth on fruit and vegetable consumption, and the fourth also addressed fat intake.

2. The telephone motivational interviewing (TMI) group, in which participants received four telephone calls based on MI. Participants chose the order of the conversation topics in the first and third call. If they chose to focus on PA in the first call, fruit and vegetable consumption was discussed in the second, and vice versa; they could also choose to discuss fat intake in the fourth call.

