### Outcome measures

#### Primary outcome measures

To measure the efficacy of TPC, TMI and TMI+TPC, the primary outcome measures of Vitalum were PA, fruit and vegetable consumption and whether participants adhered to public health guidelines with regard to these behaviors. These were measured at baseline, the intermediate telephone survey and both follow-ups (25, 47 and 73 weeks after baseline respectively). Since PA and fruit and vegetable consumption receive more attention in Vitalum, saturated fat intake was seen as a secondary outcome measure. Other studies showed that multiple-item measurements may result in people overestimating their behavior [86-95] and that adjusting the results of a multiple-item measurement with those of a single-item measurement let to reduced overestimation [86-88,92,93]. Therefore, the primary outcome measures are single – as well as multiple-item measurements, and both are combined into a measure as described below to reduce overestimation.

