#### Primary and secondary outcome analyses

Primary and secondary outcome measures will be used in the primary and secondary outcome analyses respectively. Vitalum's short-(week 47) and long-(week 73) term results will be analyzed with a 3-level multilevel mixed regression using Statistical Package for Social Sciences 15.0 (SPSS) and MLWiN. The three levels in the multilevel mixed regression were GPs, participants and measurements, given that participants are nested in GPs, and measurements (at baseline, 25, 47 and 73 weeks after baseline) are nested in participants. The quantitative dependent variables were the number of hours participants were moderately physically active per week, the number of days they engaged in moderate PA, the average daily intake of fruits, the average daily intake of vegetables, the number of days they consumed at least 2 pieces of fruit, the number of days participants consumed at least 200 g of vegetables, their total fat scores, BMIs, health-related quality of life and stage of change. The dichotomous dependent variables assessed whether participants met the public health guidelines measured with a combination of multiple items and one item, as described above. The independent variables were gender, education level, hypertension status, age, intervention group, behavioral determinants, whether they received a pedometer as a gift during the intervention period, batch number and region. Due to multiple testing, an alpha of .01 was used to evaluate results.

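### The .9 power behind the 1,600 holds for a mean difference of d = .3, but not for guideline adherence (yes/no), which is also primary: about 70% at most under a normal shift at the plan's ICC

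*Protocol article*

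**What the plan says.** Under Primary outcome measures, the protocol article says that "the primary outcome measures of Vitalum were PA, fruit and vegetable consumption and whether participants adhered to public health guidelines". Adherence is therefore primary alongside the quantities themselves. Under Primary and secondary outcome analyses it is modelled as a yes/no variable: "The dichotomous dependent variables assessed whether participants met the public health guidelines measured with a combination of multiple items and one item". Results are judged at alpha .01.

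Sample size and power gives one calculation. "The required sample size was determined using the formula for unpaired" t-tests, on the ground that every effect test in the balanced two-by-two design reduces to such a test. The inputs are "the sample size calculation was based on a small expected effect size (Cohen's d) of .3 [115]; (b) a power of .9", "an alpha of .01 to correct for multiple testing", "an intra class correlation of .02, where the correlation is based on random treatment by GP interaction" and "an expected average number of participants per general practice of 70". The result is 1,600, or 400 per group. The section gives no adherence rate and no difference in proportions, and it does not limit the .9 to some of the primary outcomes.

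Table 1 reports baseline adherence on the analysed measure in its rows for "meeting guideline combined": 0% for physical activity, 11% for fruit and 7% for vegetables.

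**The concern.** A t-test on a quantity is not the test for a yes/no outcome. When a behaviour shifts by 0.3 SD and is then cut at a threshold, the standardised effect on the resulting proportion is smaller than 0.3. It is smallest when few people pass the threshold. One power figure offered for every effect test therefore cannot describe both sets of primary measures.

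The stake is interpretation. Adherence on the combined measure is the article's own remedy for over-reporting, and it feeds the cost-effectiveness outcome that counts guidelines met. A non-significant adherence result could be taken as a null from a 90%-powered test when the real chance of detecting the planned effect was much lower.

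**Working it through.** **The plan's own figure.** Inputs from Sample size and power: d = 0.3, power .9, alpha .01, ICC .02, 70 per practice. Sidedness is not stated; two-sided reproduces the N and one-sided does not (1,377).

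- Total before clustering: 4(2.576 + 1.282)² / 0.3² = 661.
- Design effect: 1 + (70 − 1) × .02 = 2.38.
- Total: 661.3 × 2.38 = 1,574, rounded to 1,600.
- With 800 v 800, the effective number per side is 800 / 2.38 = 336. Power for a mean difference is Φ(0.3 × √(336/2) − 2.576) = Φ(1.31), about 90.5%.

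The stated N and power are reproduced for a quantitative outcome.

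**The same effect on a yes/no outcome.** Assume a normal underlying behaviour with comparison-group adherence p0. A 0.3 SD shift gives p1 = Φ(Φ⁻¹(p0) + 0.3). With n effective participants per side and p̄ the mean of p0 and p1:

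power = Φ{ [ (p1 − p0)√n − 2.576√(2p̄(1 − p̄)) ] / √(p0(1 − p0) + p1(1 − p1)) }

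Fruit at 11%: p1 = 17.7%, n = 336, and power = Φ[(1.230 − 1.277) / 0.494] = Φ(−0.095), about 46%.

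Two treatments of the practice effect are shown. The first applies the plan's ICC of .02 as it stands. The second scales it to the binary measure by ICC_b = .02 × φ(c)² / [p0(1 − p0)], where c = Φ⁻¹(p0). That scaling is an assumption and is not in the documents.

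| Comparison rate | Rate after shift | Cohen's h | Power, ICC .02 | Scaled ICC (design effect) | Power, scaled ICC |
|---|---|---|---|---|---|
| 7% (vegetables, Table 1) | 12.0% | 0.17 | 36% | .0055 (1.38) | 63% |
| 11% (fruit, Table 1) | 17.7% | 0.19 | 46% | .0072 (1.50) | 71% |
| 13.8% | 21.5% | 0.20 | 52% | .0082 (1.56) | 74% |
| 30.5% | 41.7% | 0.23 | 67% | .0116 (1.80) | 82% |
| 44% | 55.9% | 0.24 | 70% | .0126 (1.87) | 82% |

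The 13.8% and 30.5% rows are 100 minus the shares of Dutch adults that the Background cites as failing the vegetable (86.2%) and fruit (69.5%) guidelines. Over all comparison rates the maximum is about 70% (near 44%) at ICC .02, and about 82% (near 39%) with the scaled ICC.

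**Sensitivity to the conversion.** Converting d to an odds ratio by the logistic rule, exp(0.3π/√3) = 1.72, at ICC .02 gives 28% at 7%, 44% at 11%, and a maximum of 83%. The ceiling depends on the conversion, but it stays below 90% under each one.

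**What 90% would need.** At the same effective n, 90% power requires adherence to go from 7% to about 16.6%, or from 11% to about 22%.

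**Physical activity.** The baseline rate is 0% because failing this guideline was an entry condition. A 0.3 SD shift from 0% cannot be converted, so no point figure is given; the ceilings apply whatever the follow-up rate.

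**The case against.** The strongest reply is that the plan never calls .3 a shift in an underlying behaviour that is later cut. It is a generic small effect, chosen because similar studies were lacking. If a standardised effect of .3 is placed directly on adherence, the same N gives about 90%. That is arithmetically true. But it means adherence doubling or more (11% to 22%, 7% to about 17%). And under a shift of a roughly normal behaviour, one intervention effect cannot be .3 both on the behaviour and on its yes/no form. The .9 covers one set of measures or the other, not both.

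The second reply is that Table 1 rates are a poor stand-in for follow-up. They were shaped by an entry rule applied to noisy self-report, so adherence may rise even in controls. This stands. A reader might take 36% as the trial's power for adherence; the documents do not support that, because follow-up comparison rates are unknown. Higher rates raise power, but not above the ceilings.

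Third, a reader might quote about 82% as the ceiling under the plan's own practice effect. It is not: at the stated ICC of .02 the normal-shift ceiling is about 70%, and 82% needs the scaled ICC. The practice effect matters throughout. Without any, power at the baseline rates would be about 80% (vegetables) and 90% (fruit).

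Fourth, this is a condensed article, and power for further primary measures may sit in the full protocol. If the article were merely silent, that would settle the matter. It is not silent: it gives one power on the ground that every effect test reduces to a t-test. Still, it nowhere names 90% for adherence or says that a null adherence result means no effect, and neither should be attributed to it.

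Finally, the pretest covariate might seem to restore power. The article already sets that gain against 20% dropout, and the baseline combined physical activity measure is 0% for everyone, so it has no variance to adjust with.

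**Conclusion.** The point holds as one about the scope of the power statement. A reader might infer that 1,600 was miscalculated; it was not, and the calculation is sound for a quantitative outcome at d = .3.

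For adherence, the shortfall against .9 is at least 20 percentage points (90 − 70) under the normal shift at the plan's ICC, and about 44 to 54 points at the baseline fruit and vegetable rates (90 − 46 and 90 − 36). With the scaled ICC it is at least 8 points, and about 19 to 27 points at the baseline rates.

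These sizes rest on a normal underlying behaviour shifted by 0.3 SD, two-sided alpha .01, 800 v 800 as the plan's main-effect comparison implies, 70 per practice, and no allowance for dropout or pretest adjustment, as in the plan's own calculation. Treating combined adherence as a single cut is an approximation, since it requires passing both a multiple-item and a single-item criterion. That the power falls short is firm under every conversion of a 0.3 SD behavioural effect tried here with a practice effect included; the exact percentage is not.

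**What to change.** In Sample size and power, state that the .9 at d = .3 applies to the quantitative primary measures only. Add the power for dichotomous adherence under the same 0.3 SD effect as a range over comparison rates (for example 7% to 44%), naming the conversion and the ICC used: about 36% to 70% at ICC .02, and about 63% to 82% if the ICC is scaled to the binary measure. Say that the physical activity comparison rate at follow-up is unknown.

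In Primary and secondary outcome analyses, state that adherence effects are reported with confidence intervals and that a non-significant adherence result is not read as a 90%-powered null.

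The cost is a few sentences. No participant, test or alpha level changes, which matters because 1,629 people are already randomised. The downside is a less favourable stated power for adherence.

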## Methods/Design

### Participants and recruitment

Vitalum was approved by the Medical Ethics Committee of Maastricht University and the University Hospital Maastricht, and is registered with the Dutch Trial Register (NTR1068).

In 2004 and 2005, Dutch general practices (GPs) from the southern Netherlands were invited to join in the recruitment of 1,600 participants via a registration network (Registration Network Family Practices; RNH) [62,63] or by personal invitation. Twenty-three agreed to participate; 19 from the province of Limburg and 4 from Brabant. GPs that declined were participating in other research trials or had too little time.

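### The 90% power at N = 1,600 ignores that the treatment-by-practice variance is estimated from about 23 practices; with practice-based degrees of freedom power is about 85% (about 89% if that variance is pooled)

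*Protocol article*

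**What the plan says.** Under Sample size and power, the protocol article states: "The required sample size was determined using the formula for unpaired" t-tests, on the ground that "each effect test in a balanced 2 × 2 between-subject design" reduces to such a test. The inputs are "a small expected effect size (Cohen's d) of .3", power of .9, "an alpha of .01 to correct for multiple testing", "an intra class correlation of .02, where the correlation is based on random treatment by GP interaction", and "an expected average number of participants per general practice of 70". The section adds that a random practice main effect does not matter when persons are randomized within practices. Dropout and the gain from a pretest covariate are left out of the calculation; the text argues that 20% dropout is offset if pretest and posttest correlate .5. The result is 1,600, or 400 per group.

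Under Participants and recruitment, the number of practices is given: "Twenty-three agreed to participate; 19 from the province of Limburg and 4 from Brabant".

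Under Primary and secondary outcome analyses, a three-level mixed regression (practices, participants, measurements) is planned, and "Due to multiple testing, an alpha of .01 was used to evaluate results". That section names no reference distribution and no degrees of freedom, and does not say whether a random treatment-by-practice term is fitted.

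**The concern.** When treatment effects differ randomly between practices, the error term for an average treatment effect includes that between-practice variation. A design effect allows for the added variance, but not for the variance having to be estimated from few units. With about 23 practices the reference distribution is a t with far fewer degrees of freedom than 1,600 persons would suggest. At alpha .01 this penalty is larger than at .05.

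Under the plan's own assumption, then, 90% power and alpha .01 may not both hold. Either power is below the stated figure, or, if a normal cut-off is applied, the .01 level is exceeded. That level is the only multiplicity control the article states, and it has to cover several outcomes, three factorial effects and two follow-ups.

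**Working it through.** **Inputs** (Sample size and power, unless noted): d = .3; power .9; alpha .01, taken as two-sided because a one-sided test gives 1,380 and does not reproduce the stated N; ICC .02; 70 per practice; each main effect compares 800 with 800; 23 practices (Participants and recruitment), which agrees with 1,600/70 = 22.9.

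**1. The plan's own figure.**
- Per side: 2 × (2.576 + 1.282)² / .3² = 330.7, so about 661 in total.
- Design effect: 1 + (70 − 1) × .02 = 2.38.
- N = 661.3 × 2.38 = 1,574. Rounding to 331 per side first gives 1,576.
- With a t-test on person-level df: 333 per side, and 666 × 2.38 = 1,585.

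Both are within 3% of 1,600. The plan's N therefore uses a critical value of about 2.58.

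**2. Where the variance comes from.** With K practices of 70, the variance of the estimated difference is 4 × (.98/70 + .02)/K = 4 × (.014 + .020)/K. More than half of it is the between-practice part. For K = 1,600/70 = 22.86 the variance is .00595 and the standard error .0771. The noncentrality is .3/.0771 = 3.89 (3.90 for K = 23).

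**3. Power at d = .3 under different references, with no dropout and no pretest gain.**

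| Reference | Critical value | Power | True alpha if 2.576 is used |
|---|---|---|---|
| Normal | 2.576 | 90.5–90.8% | 1.0% |
| t, 22 df (own interaction variance for each contrast) | 2.819 | 84.5–84.8% | 1.72% |
| t, 66 df (one variance pooled over three contrasts) | 2.652 | 88.8–89.0% | 1.22% |

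The ranges run from K = 22.86 to K = 23. Simulating contrasts for 23 practices gave 84.7% power and 0.99% size for the 22-df test, and 1.72% size with the normal cut-off. At the 1,629 actually randomized, 22-df power is 85.0–85.3%.

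**4. Equivalent statements at 22 df.** The effect detectable with 90% power is d = 0.32. Holding d = .3 and 70 per practice, 90% power with practices-minus-one df needs 26 practices (N = 1,820).

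**5. The plan's dropout scenario (20% dropout, r = .5, 22 df).** There are now 56 per practice, and the pretest multiplies a variance by 1 − .5² = .75.
- Pretest reduces only person-level variance: 4 × (.98 × .75/56 + .02)/K, power 85.6–85.8%.
- Pretest also reduces the interaction variance: 4 × .75 × (.98/56 + .02)/K, power 91.5–91.7%.
- Dropout with no pretest gain: 4 × (.98/56 + .02)/K, power about 80%.

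**The case against.** The strongest case against has four parts.

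*Nothing in the sample-size section contradicts itself, and N reproduces.* This is correct. The section names a t-test formula and never says that a normal value was used; that is inferred from the arithmetic. But person-level t gives practically the same N, and neither version reflects 23 practices.

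*22 df is a modelling choice.* This stands. The plan gives a single ICC for all three factorial effects, so a common interaction variance is a possible reading, and at 66 df most of the gap closes. A reader might infer that the trial simply has 85% power. The documents do not support so firm a figure. Reducing each effect to its own two-group test fits 22 df better, but the article states neither.

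*The ICC could mean something else.* If .02 were the correlation within one arm of one practice, with 35 persons per cluster, power would exceed 95% even at 22 df. But the design effect would then be 1 + 34 × .02 = 1.68 and N about 1,111, which is not the plan's figure. The stated 1,600 requires the variance used here.

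*The alpha argument is hypothetical, and the choice of df is commonly left to an analysis plan.* Largely accepted. A reader might infer that the trial's real type I error is 1.7%. That would need an analysis that fits the interaction and then uses a normal cut-off, and the article states neither. The missing df rule is not in itself an error; the point rests on the stated power.

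The shortfall is also small beside the uncertainty in the inputs: an ICC of .015 would give about 90.5% at 22 df. That bears on how serious the point is, not on whether the stated power follows from the stated inputs.

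**Conclusion.** The concern holds in a bounded form. On the plan's own inputs, and leaving out dropout and the pretest as the plan does, 90% power at 1,600 is not reached once the treatment-by-practice variance is estimated from about 23 practices. Power is about 85% with a separate interaction variance for each contrast and about 89% with a pooled one, so the loss is between roughly 1 and 6 points. In the plan's dropout scenario, 22-df power is about 86% or about 92%, depending on whether the pretest also reduces the interaction variance, which the article does not say.

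Inflation of alpha to about 1.7% (22 df) or 1.2% (66 df) is conditional on a normal reference with the interaction in the model. It is a risk to close off, not a stated fault.

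These results assume a two-sided test and practices of equal size. Practice sizes are not given, and unequal sizes would lower power further.

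**What to change.** In Sample size and power, restate the power at d = .3 for 23 practices as about 85% (up to about 89% if one interaction variance is pooled over the contrasts), or give the detectable effect as d of about 0.32 at 90% power. Say which variance assumption is meant.

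In the analysis, test intervention effects that carry a random practice-level component against a t reference with practice-based df, or with Satterthwaite or Kenward-Roger df, rather than a normal one.

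The cost is one restated figure and one sentence. The downside is a less favourable stated power and slightly wider intervals. Recruitment is complete, so no change to the sample is asked for.
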